### Intervention

The OHP is a person-centered model that focuses on health as defined by patients. It aims to support people with mental or physical illness by using a collaborative therapy–based self-efficacy intervention [55,75-78]. The program addresses psychological and physical dimensions of health [60], is flexible, and can be delivered by a range of practitioners. It can also be delivered at all stages of the care trajectory; in inpatient and outpatient settings, at homes, or by video conferencing, and to groups or to individual patients [77]. By enhancing self-efficacy and self-management skills, the program works on shifting the focus of an individual’s illness from being “dependent on services” to being “supported by services” [78], which is thus anticipated to reduce pressure and financial demands on health care systems.

The OHP can be delivered in 8- or 5-session sequential formats, with both types of delivery including a follow-up “booster session” [55] [77-80]. It offers its users (ie, facilitators and participants) a written booklet that includes different skills and information to support self-efficacy, besides regular reviews of previous sessions to follow progress [55]. In this trial, recognizing that fatigue is a core component, the LC-OHP will be delivered in 5 sequential sessions. The program’s key elements are summarized in Table 2.

**Table 2 table2:** LC-OHP^a^ sessions.

Session	Title	Content
1	Optimal health	What is optimal health? Optimal health wheel
2	I-Can-Do-Model	Strengths and vulnerabilities Stressors and strategies Health plans 1 and 2
3	Factors of well-being	Medication and metabolic monitoring Collaborative partners and strategies Health Plan 3
4	Visioning and goal setting	Defining change Orientation and preparation Creative problem-solving and goal setting Reflection and celebration
5	Building health plans	Health plans 1, 2, and 3 My health journal
Booster	Reflecting on the learning in the transformational journey to sustain well being	Reflecting on learning in the transformational journey to sustain well-being

^a^LC-OHP: Long COVID Optimal Health Program.

Sessions will be delivered weekly with a booster session to be held 3 months after the last session. The booster session will target reviewing health plans and reflecting on achievements made toward health-related goals. Sessions will be held either in a 1:1 encounter with the facilitator, or in groups, or using a mixture of both, depending on participants’ preferences. Each 1:1 session will last up to one hour, with breaks provided upon participant’s request, and if necessary, the session can be completed at another time. Group sessions will last up to 90 min, and breaks will be provided upon request. Sessions will be held online (using a convenient platform) or by telephone (to those who do not have access to online facilities). Sessions will be audio-recorded to be checked by another member of the research team to confirm fidelity of program delivery. Participants can contact facilitators between the sessions if they have any questions or wish to change the time for the next session.

Facilitators have received prior training in delivering the program during a 2-day workshop delivered by one of the investigators ([name]) who developed the OHP program. Regular supervision will also be provided to facilitators to ensure fidelity with program delivery and to discuss any concerns. Additionally, a fidelity checklist will be completed by the facilitator after the end of each session to ensure all core components of each session have been covered. The checklist will also be reviewed by another member of the research team to ensure fidelity.

### Quantitative Data Collection

Following participation and baseline data collection, the research team will contact participants at 3-month intervals after randomization at a prearranged time to complete the questionnaires detailed in Table 1. At the end of the trial, participants in the intervention group will be asked to evaluate the LC-OHP by completing the Course Experience Questionnaire.

### Qualitative Interviews

After the end of the trial, participants allocated to the intervention group will be invited to participate in a semistructured telephone interview conducted by an independent researcher (not the OHP facilitator). The interview will target exploring participants’ experience with the LC-OHP, identify their views on the program, and share any suggestions for improving the program for the future. Interviews will be audio-recorded and will be conducted at a time convenient to the participant. Interview duration will last up to 30 min (a max of 40 min if a participant requests more time) and will be guided by a topic guide developed by the research team. Participants will be interviewed until data saturation is reached. Textbox 1 shows a summary of the interview topic guide list.

Summary of the interview topic guide list.
**Main questions**
Can you please tell me a little bit about why you agreed to take part in the study?Describe your experience of being involved in the program.What do you think about the materials and support provided throughout the program?Do you feel that there may be changes that could be made to the program? What, how, and why?

### Internal Pilot

The trial will start with an internal pilot, with the first 2 participants receiving a 1:1 session delivery. These participants will have a short interview (10 min) at the beginning of each session by the facilitator to identify their views about the previous session with respect to the program’s materials and to inform any necessary refinements before starting the program with other participants. The program will start 2 weeks following the internal pilot in order to give enough time for any modifications to be implemented. Figure 1 presents a flowchart of the trial process.

**Figure 1 figure1:**
[figure not shown]
Participants' flow in the study. OHP: Optimal Health Program.

### Participant Withdrawal

Participants can leave the study at any time without their care being compromised. All data collected from participants prior to withdrawal will be included in the analysis.

Participants’ withdrawals will be noted, and reasons will be classified under the following categories: (1) illness or death; (2) dropout or relocation; (3) loss of contact; and (4) failure to return the questionnaire.

Additionally, for the purpose of ensuring fidelity, the trial’s research team will interview a sample of participants who withdrew from the intervention to identify reasons behind their withdrawal, and to collect any suggestions that may improve the program for future participants. The withdrawing participants will be free to decline this interview without their usual care being affected.

### Data Analysis

Quantitative data analysis will be performed using SPSS (IBM Corp). Descriptive data will be presented using means, interquartile range, and percentages. Differences between the groups will be compared using appropriate inferential tests.

For the qualitative data, interviews will be recorded (with informed consent), transcribed verbatim, coded, and thematically analyzed (using an inductive thematic analysis approach) to identify common emerging themes [81]. Transcripts will be continuously revisited, and the accuracy will be verified by listening to the recordings and comparing them with the transcripts. Coding of data will be conducted using NVivo (QSR International), and codes will be checked by another member of the research team to ensure appropriate and consistent coding process. Any disagreements will be resolved by consensus, and by referring to the transcripts and original recordings.

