**Methods:**

This is a feasibility randomized controlled trial that will be running from November 2021 to February 2023. Eligible participants aged 18 years or older who are experiencing symptoms of long COVID will be identified through their secondary practitioners with recruitment to be undertaken by the research team. A total of 60 participants will be randomized into a control (usual care) or an intervention (LC-OHP) group. Outcomes will be feasibility and acceptability of the program (primary); and efficacy of the LC-OHP in improving anxiety, depression, fatigue, self-efficacy, and quality of life (secondary). Up to 20 participants will be interviewed at the end of the trial to explore their experience with the program. Quantitative data will be analyzed using SPSS, and differences between groups will be compared using inferential tests where appropriate. Qualitative data will be transcribed and thematically analyzed to identify common emerging themes.

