#### Secondary Objectives

The secondary objectives are to evaluate the preliminary efficacy of the LC-OHP in improving quality of life, depression and anxiety, fatigue, and self-efficacy in people with long COVID, compared to usual care.

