#### Sample Size

A total of 60 patients will be recruited to the trial, with 30 randomized to the intervention or control group. The sample size has been determined according to the recommendations that at least 30-35 patients be included per group for pilot and feasibility studies [63-66].

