## Results

This is an ongoing study, which began in November 2021. The outcomes will be feasibility and acceptability of the program (primary); and its efficacy on improving anxiety, depression, fatigue, self-efficacy, and quality of life (secondary). It is hypothesized that the LC-OHP will be acceptable by participants, will improve their health and psychosocial functioning, and will enable them to gain better understanding of this condition, increasing patient self-efficacy of their symptoms.

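### Between-group tests are the only stated comparison of the secondary outcomes in a 60-person feasibility trial; exploratory, baseline-adjusted estimates with 95% confidence intervals would serve its purpose better

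*Protocol article*

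**What the plan says.** The Data Analysis section gives two sentences of quantitative method beyond naming the software. The first is "Descriptive data will be presented using means, interquartile range, and percentages". The second is "Differences between the groups will be compared using appropriate inferential tests". The abstract repeats the second in a softer form: "differences between groups will be compared using inferential tests where appropriate".

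The Secondary Objectives are to "evaluate the preliminary efficacy of the LC-OHP in improving quality of life, depression and anxiety, fatigue, and self-efficacy", against usual care. The Results section adds an expectation: "It is hypothesized that the LC-OHP will be acceptable by participants, will improve their health and psychosocial functioning".

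The sample size rests on neither an effect size nor power. The Sample Size section says "A total of 60 patients will be recruited to the trial, with 30 randomized to the intervention or control group", and justifies this by recommendations that "at least 30-35 patients be included per group for pilot and feasibility studies".

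Table 1 lists five questionnaires (PHQ-9, GAD-7, GSE, EQ-5D-5L and FAS), to be completed at baseline, 3 months and 6 months. The section on randomization places the baseline questionnaires before allocation. Future Directions describes the findings as pilot data for a later, fully powered trial.

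**The concern.** The article commits to testing differences between arms, and this is the only comparison it states for the outcomes on which it hopes to show improvement. A test answers whether a difference can be told apart from zero. With 30 per arm chosen for feasibility, that question will usually be answered badly in both directions. Across several scores and two time points, one significant result is easily produced by chance. A non-significant result leaves a worthwhile benefit entirely possible.

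The later trial needs something else from these data: how large the difference might be, and how uncertain that is. An estimate with its interval gives this directly and does not invite a verdict on efficacy. The stated hypothesis of improvement increases the risk that test results will be read as such a verdict.

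**Working it through.** **Inputs from the article.** 60 participants, 30 per arm; five questionnaires; follow-up at 3 and 6 months; baseline scores obtained before randomization.

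**Assumptions not in the article.** Two-sided 5% level; 20% loss to follow-up (24 per arm) as an alternative to full retention; correlation between test statistics of 0 to 0.7; baseline to follow-up correlation (rho) of 0.3, 0.5 or 0.7.

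**1. The plan's own figure.** 2 × 30 = 60, which reproduces the stated total. Thirty per arm is the lower end of the recommended 30 to 35. The article gives no significance level, power, effect size or SD, so there is no power calculation to check.

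**2. Number of comparisons (derived).** Five questionnaires × 2 times = 10. Counting the EQ-5D-5L visual analogue scale as a separate score gives 6 × 2 = 12.

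**3. Chance of at least one false positive.** With no true effect and k independent tests it is 1 − 0.95^k:
- k = 12: 1 − 0.95^12 = 0.460
- k = 10: 1 − 0.95^10 = 0.401

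Scores from the same people are correlated, so independence is the upper end. Simulating equally correlated normal test statistics (400,000 draws, any value beyond ±1.96) gives:

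| Correlation | 12 tests | 10 tests |
|---|---|---|
| 0 (formula) | 46% | 40% |
| 0.3 | 40% | 35% |
| 0.5 | 32% | 29% |
| 0.7 | 23% | 21% |

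**4. Power of an unadjusted two-sample t test at 0.5 SD.** The noncentrality is 0.5 × √(n/2).
- 30 per arm: 0.5 × √15 = 1.94, 58 degrees of freedom, power 48%
- 24 per arm: 0.5 × √12 = 1.73, 46 degrees of freedom, power 40%

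The difference detectable with 80% power is 0.74 SD at 30 per arm and 0.83 SD at 24 per arm. By the normal approximation, 80% power at 0.5 SD needs 2 × (1.96 + 0.84)² / 0.5² ≈ 63 per arm.

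**5. Precision, with and without baseline adjustment.** The 95% half-width in SD units is 1.96 × √(2/n) × √(1 − rho²), with rho = 0 for no adjustment.

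| | Unadjusted | rho 0.3 | rho 0.5 | rho 0.7 |
|---|---|---|---|---|
| 30 per arm | 0.51 | 0.48 | 0.44 | 0.36 |
| 24 per arm | 0.57 | 0.54 | 0.49 | 0.40 |
| Factor √(1 − rho²) | 1 | 0.954 | 0.866 | 0.714 |
| Narrowing | none | 5% | 13% | 29% |

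Without adjustment and with everyone followed up, an observed difference of exactly zero would still have an interval reaching about 0.5 SD in each direction.

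**6. Does adjustment supply the missing power?** By the normal approximation, power at 0.5 SD with 30 per arm goes from 49% to 53%, 61% and 77% for rho of 0.3, 0.5 and 0.7. It stays below 80% throughout.

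**The case against.** The best defence is that the article never claims power for efficacy. Feasibility and acceptability are primary, efficacy is called preliminary, and the results are meant to feed a larger trial. Showing low power then only restates what a feasibility trial is. Tests and intervals also come from the same model, so a promise of tests does not rule out intervals. This defence stands as far as severity goes: the primary objectives are untouched. It does not remove the point, because testing is what the article chose to state, alongside a hypothesis of improvement.

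Four stronger readings are tempting, and the article supports none of them.

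- **That baseline scores will be ignored.** The article does not say so. Analysis of covariance would count as an appropriate inferential test, and the choice of model and covariates is commonly left to a full protocol or analysis plan, which is not shown. Baseline adjustment is therefore part of the recommendation, not a fault found.
- **That testing contradicts the Participant Withdrawal section.** That section says "All data collected from participants prior to withdrawal will be included in the analysis". A 3-month comparison would use the 3-month data of someone who withdrew later, so nothing conflicts. A mixed model would only use those data more fully.
- **That 12 tests are planned.** The count comes from Table 1 and the visit times. The qualifier in the abstract leaves open which outcomes will be tested.
- **That a test result decides whether the larger trial goes ahead.** No section makes that link.

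**Conclusion.** The point holds at moderate severity. The stated analysis of the secondary outcomes is testing between arms, in a sample chosen by a feasibility rule, next to a hypothesis of improvement. If every score were tested at both times, the chance of at least one false positive would be about 23% to 46% for 12 tests and 21% to 40% for 10. Power for a 0.5 SD effect is about 48% with full retention and 40% with 20% loss. Test results would thus tell the reader little in either direction.

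The power figure at full retention needs only the stated sample size, a 5% level and the chosen effect size. The error rates also depend on the assumed correlation and on how many comparisons are actually tested. The gain from adjustment depends on a correlation the article does not give. The main reason for the change is the move from tests to intervals; adjustment is a useful addition that leaves the trial unpowered for efficacy.

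**What to change.** In the Data Analysis section, replace the sentence on inferential tests with wording such as:

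> The secondary outcomes are exploratory. For each score, the mean difference between arms at 3 and 6 months will be estimated with a 95% confidence interval, adjusted for the baseline score by analysis of covariance or a linear mixed model, with participants in the arms to which they were randomized. No claim of efficacy will be based on significance tests.

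Bring the matching sentence in the abstract into line. In the Results section, keep the expectation on acceptability but turn the hypothesis of improvement into an aim: to estimate the difference between arms in each score, and its uncertainty, to inform the design of a larger trial.

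The cost is a few sentences. No new data are needed, because baseline scores are already collected before randomization, and both models run in the named software. The small downside is giving up a headline of statistical significance.

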### Data Management and Monitoring

All data collected from participants will remain strictly confidential, and all participants will be pseudonymized and coded with a study number. Data will be securely stored at a central computer drive accessible only to members of the research team. Principles of the General Data Protection Regulation 2018 will be followed with respect to data storage, processing, and destruction. Any paper documents will be stored in a securely locked filing cabinet located at the Integrated Care Academy at the University of Suffolk, accessible only to members of the research team.

A Data Management Committee (DMC) is set for the trial and will include the sponsor, 2 clinicians, 2 independent researchers, and 2 members of the public. The committee will meet at least 3 times (at the start, middle, and end of the trial) and as needed. The DMC will oversee all aspects of the study and will monitor the trial’s progress and deadlines adherence, ensuring participant safety is maintained and agreeing on any amendments to the protocol. Any amendments conducted will be notified to ethical committees.

The trial will be prematurely terminated if severe and unacceptable safety risks occur. Adverse events will include any unfavorable and unintended events experienced by a participant during the study that are reported by the participant or observed by the investigator or medical staff. Serious adverse events will be any untoward medical occurrence that could result in death, hospitalization or prolongation of existing hospitalization, persistent or significant disability or incapacity, or a congenital anomaly or birth defect. Adverse events and serious adverse events will be registered and presented to the DMC to be reviewed. The DMC will have the power to stop the trial on safety grounds. However, it is highly unlikely for early termination as the OHP has been previously used with people with chronic medical conditions and has been proven effective, without untoward outcomes.

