A recent systematic review, which included 25 studies with 5440 participants, reported the frequency of long COVID to be up to 80% of the included population [17]. Another study showed that some symptoms persisted 3 months post hospital discharge [24]. Moreover, it seems that anyone can develop long COVID, including young people with no preexisting health conditions [18,25]. In the United Kingdom, the Office of the National Statistics and the UK COVID-19 symptom study app show that 1 in 5 people have COVID-19 symptoms that persist after 5 weeks, and 1 in 10 have symptoms that persist longer than 12 weeks [8,26]. To date, more than 8 million cases of COVID-19 have been confirmed in the United Kingdom [5], with more than 2 million people reporting they may have had long COVID [27], but the number is expected to increase as the virus is still active in the community.

Symptoms of long COVID vary between individuals. It seems to affect multiple organ systems in the body, and patients can present with single, multiple, constant, transient, or fluctuating symptoms [12,28], in a continuous or a relapsing and remitting course. According to a recent meta-analysis, the five most commonly reported symptoms are fatigue (58%), headache (44%), attention disorder (27%), hair loss (25%), and dyspnea (24%) [13]. Fatigue was found to be independent of the severity of the initial viral infection and to develop irrespective of a preceding hospitalization [29]. Long COVID represents a challenge for both the patient and the health care provider as it can be difficult to diagnose with certainty and may influence the doctor-patient relationship and trust [30]. Other reported manifestations of long COVID include cough, joint pain, chest pain, and low-grade fever [8,31,32].

Encountered neuropsychiatric symptoms include anosmia, brain fog, and neuropathy [33,34]. COVID-19 doubles the risk of developing a psychiatric disorder [35]. Anxiety, depression, or posttraumatic stress was manifest in 56% of patients with long COVID [36]. Social isolation, decreased physical activity, changed habits, as well as social and economic insecurity that are associated with the pandemic may contribute to developing the physical and psychological symptoms of long COVID [17,37].

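### Serious adverse events are defined by what an event could lead to, not by what it did lead to, so the serious/non-serious split depends on the assessor in an unblinded trial

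*Protocol article*

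**What the plan says.** The safety rules stand in Data Management and Monitoring.

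- Adverse events are defined broadly: "Adverse events will include any unfavorable and unintended events experienced by a participant during the study", whether the participant reports them or the investigator or medical staff observe them.
- The serious subset is then defined: "Serious adverse events will be any untoward medical occurrence that could result in death, hospitalization or prolongation of existing hospitalization". The sentence continues with "persistent or significant disability or incapacity, or a congenital anomaly or birth defect".
- On use: "Adverse events and serious adverse events will be registered and presented to the DMC to be reviewed".
- On stopping: "The trial will be prematurely terminated if severe and unacceptable safety risks occur", and "The DMC will have the power to stop the trial on safety grounds". No number or rate of events is attached to either statement.

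Two other parts bear on the point. The Background gives dyspnea in 24% of patients among the five commonest symptoms, and adds: "Other reported manifestations of long COVID include cough, joint pain, chest pain, and low-grade fever". It also describes symptoms that may fluctuate or relapse and remit. The section on Randomization, Allocation, and Blinding says that neither the research team nor the participants can be blinded.

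**The concern.** A seriousness criterion is useful when two people who see the same event record give the same answer. Whether someone died or was admitted is a fact. Whether an event might have led to death or admission is an opinion, and the article sets no degree of likelihood for it.

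This matters more here than in many trials. The disease fluctuates, and some of its listed symptoms can plausibly raise the question of admission. Knowledge of the arm is available to the research team. The arms also differ in how often the team speaks to participants. At stake is whether the serious label shown to the DMC, and any summary of it by arm, means the same thing for every participant.

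**Working it through.** The article gives no serious-event rate, expected count or numerical boundary, so there is no figure to reproduce. The check is a reading of the rule against the setting in which it will be applied.

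**1. Reach of the verb.** The sentence has one verb phrase with *could* in it, followed by a list: death, hospitalization or its prolongation, disability or incapacity, congenital anomaly or birth defect. Every item hangs on that verb. Nothing later in the section narrows it.

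**2. The rule applied to one event.** Take a participant whose breathlessness worsens for some days, who stays at home and who returns to the previous state.

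- Rule as written: an assessor who thinks admission was possible records a serious event; one who thinks it was not records a non-serious event. Neither has departed from the text.
- Outcome-based rule: no death, no threat to life at the time, no admission, no persistent or significant disability. Both assessors record a non-serious event.

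**3. Which symptoms this touches.** Of the symptoms named in the Background, dyspnea and chest pain are the clearest candidates. Hair loss, mild headache or attention disorder would not plausibly lead to a listed outcome. So some worsening episodes may qualify, not long COVID symptoms in general.

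**4. Opportunity for events to be heard about, by arm.** From Intervention, Table 1 and Quantitative Data Collection, the scheduled contacts after randomization are:

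- LC-OHP arm: 5 weekly sessions + 1 booster + 2 questionnaire contacts (3 and 6 months) = 8. The end-of-trial evaluation and interview are additional, and participants may contact facilitators between sessions.
- Control arm: 2 questionnaire contacts (3 and 6 months) = 2.

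Deaths and admissions are comparatively likely to come to light under either schedule. An episode managed at home that only might have led to admission is more likely to be mentioned, and then graded, where there are 8 contacts than where there are 2.

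**5. Life-threatening events.** There is no separate criterion for these. They are reached only because such an event could result in death. A fix that merely changed the verb would drop those that the participant survived without another listed outcome, so the criterion has to be added at the same time.

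**The case against.** The strongest reply is that this is loose drafting with little consequence. A broad definition errs towards reporting. All adverse events, serious or not, go to the DMC, whose members include 2 clinicians, so in a trial of 60 an admission or death would not be hidden behind a broad label. Safety is neither a primary nor a secondary objective. The article does not say who grades seriousness or whether DMC members know the allocation. It also condenses a fuller protocol, where the handling of expected symptoms may be set out.

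Most of this stands, and it limits the point. It does not remove it: the article states a complete rule, and that rule gives inconsistent answers as worded. Silence on expected symptoms is not the complaint.

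Four stronger readings are tempting, and the document does not support them.

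- *That ordinary long COVID symptoms, or almost any relapse, are serious events.* The rule still needs an untoward occurrence, adverse events must arise during the study, and ongoing symptoms are an entry condition. The disability criterion requires persistence or significance. The article describes multisystem disease with a significant effect on functioning, but does not call it disabling.
- *That the DMC's stopping decision rests on an inflated count.* The committee reviews events and judges risk; no count or threshold is stated.
- *That true signals would be diluted.* The DMC receives every registered event and can see for itself which involved an admission or death.
- *That the excess can be computed.* One could take 0.24 × 60 = 14.4 participants with dyspnea and suppose that 25% to 75% have one episode, giving 3.6 to 10.8 extra serious events. This assumes both the episode rate and that every episode is graded serious, which is the matter in question.

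**Conclusion.** The point holds as a defect of wording with a practical effect. Seriousness is set by hypothetical outcome, so classification depends on the assessor, and the open-label design with unequal contact leaves room for it to differ between arms. Its size cannot be derived from the document, and no stated decision rule changes.

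The conclusion rests on the sentence being applied as printed and on grading being done by, or with information from, the unblinded research team. If graders are in fact blinded to arm, the inconsistency remains, but deliberate or unconscious grading by arm falls away. Unequal opportunity to hear of events would persist. A full protocol with an outcome-based definition would already meet the point, and the article's sentence would then only need to match it. The correction is worth making because it is cheap and because the article intends these data to support a larger multisite trial, where more assessors would apply the same rule.

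**What to change.** Reword the definition so that an event is serious if it:

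- results in death;
- is life-threatening at the time it occurs;
- requires hospitalization or prolongs an existing stay;
- results in persistent or significant disability or incapacity, judged as a change from the participant's baseline; or
- is a congenital anomaly or birth defect.

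Continue to register every other event as an adverse event and present it to the DMC, so that nothing now seen by the committee is lost.

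The cost is one sentence in the protocol and a matching change to the event form, with notification to the ethics committees as the article already provides for amendments. No participants, visits or assessments are added. The downside is that fewer events may carry the serious label. Because the trial has already started, events graded under the present wording should be re-graded so that one rule applies throughout.
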